## **1.0 Introduction**

Stroke is a challenging neurological disorder worldwide and remains the second leading cause of death and disability in the world (Feigin et al. 2022). Currently, 16.9 million people worldwide suffer from stroke each year, with an incidence rate of 258/100,000 person-years (Béjot et al. 2016). The incidence of stroke in mainland China in 2020 is 505.2/100,000 person-years (Tu et al. 2023). In 2017, there were 1.12 million stroke cases in the European Union (Wafa et al. 2020). Strokes may cause extensive neurological damage, leading to a wide range of rehabilitation needs and challenges, with upper extremity dysfunction being particularly common (Raghavan 2015). This dysfunction can affect quality of life (Carod-Artal & Egidio 2009).

A pressure garment is an external tool made of elastic material that applies pressure to improve swelling, inhibit scarring, and enhance motor performance (Anzarut et al. 2009). Because of its effect of reducing muscle tone, it is now also widely used in the rehabilitation of children with cerebral palsy (Gerard et al. 2022). However, in the field of stroke, the therapeutic effect of pressure garment has not yet been more fully investigated. A paper published by Gracies et al. (2000) mentions that pressure garment has an antispastic effect on the wrists and fingers of hemiplegic patients., thus, they can help patients with severe spasticity or painful swelling of the extremities. A randomised controlled trial by (Ooi et al. 2020) showed no difference between intervention group that received a pressure garment and control group that received no pressure garment in terms of arm spasticity and function in the early post-stroke period; however, verbal feedbacks provided by the intervention group patients were generally positive, especially pressure garment allowed greater finger extension, facilitating better grasp and release. The authors justified inadequate wearing time, inappropriate pressure compression related to design and length of the pressure garment, and small sample size as the primary reasons that resulted in these unfavourable outcomes. Therefore, their recommendation for future studies included focusing on improving the design of the pressure garment, alongside increasing wearing time and sample size.

Based on the given justifications and recommendations, it is salient that the

clinical applications of pressure garment after stroke are yet to be fully explored and valued. Therefore, an in-depth and comprehensive study using a mixed methods design is needed. This proposed study will involve using multicentre double-blind randomized controlled trial, photovoice, and semi-structured interview to determine the effects of different pressure garment on sensorimotor functions and quality of life among stroke patients in Weifang, Shandong Province, China. Findings of this study are expected to be of value for stroke rehabilitation, primarily in accelerating the rehabilitation process and optimizing stroke recovery. This study is expected to promote evidence-based practice, aligning with China governmental policy “Healthy China 2030”. For Malaysia, this research is aligned with the “National Policy for Quality in Healthcare 2022-2026” that emphasizes of providing high quality healthcare that is safe, effective, and efficient to patients.

## **2.0 Problem Statement**

Stroke can lead to sensorimotor dysfunction, impaired sensation, and an imbalance in muscle tone between the flexor and extensor systems, causing the elbow, wrist, and fingers to assume a flexed position (Hatem et al. 2016). These disturbances may result in an inability to grasp and release, impairing the ability to perform functional activities. Given that such limitations may lead to a reduced quality of life, effective upper extremity stroke rehabilitation is needed. Regaining upper extremity sensorimotor functions after stroke has always been a complex and challenging task. Patients often need multiple methods to facilitate recovery. Pressure garment, although clinically has been used to reduce spasticity in the rehabilitation of children with cerebral palsy, it is only be used very limitedly in stroke rehabilitation. This is basically due to limited evidence-based research to support positive effects of pressure garment for stroke recovery. Particularly, previous studies have sample sizes, inappropriate garment design and wearing duration. Therefore, by referencing Ooi et al.’s (2020), there are a few issues that need to answered. Typically, pertaining to effectiveness of different garment designs (varying in terms of fabric layer and circumferential reduction),

amount of the sensorimotor functional changes that can be detected in the upper extremity, alongside changes of quality of life after pressure garment application. It is also important to explore the perceptions of stroke patients on pressure garment wearing experience, needs, challenges, and satisfaction as well as perceptions of treating therapists regarding the clinical values of pressure garment in the treatment for stroke.

### **3.0 Research Significance**

Aligning with China's governmental policy "Healthy China 2030" and Malaysia's "National Policy for Quality in Healthcare 2022-2026" that emphasizes providing high quality healthcare that is safe, effective, and efficient to patients, this study is significant as it will promote stroke rehabilitation for the optimization of stroke recovery. By studying the effect of pressure garment on upper extremity dysfunction, healthcare professionals can make more targeted treatment choices and improve the chances of successful rehabilitation. Specifically, the success of improving patients' upper extremity dysfunction, followed by daily functioning and quality of life. This study will also expand the clinical values of pressure garment. If pressure garment is found to be effective in the rehabilitation of stroke patients, it can help to further expand the clinical values of pressure garment beyond its conventional usages, i.e., for scar and oedema management.

Most importantly, examining the effects of pressure garments empirically via combination of both quantitative and qualitative methodologies will improve the robustness of the study findings, in line with the need of implementing evidence-based practice.

### **4.0 Research Questions**

General Research Question:

What are the effects of different finger-to-above-elbow (long glove) pressure garments with varying fabric layer and circumferential reduction on sensorimotor functions and quality of life among stroke patients during the 8 weeks of application,

and what are the perceptions of stroke patients and treating therapists on various issues relating to pressure garment application in stroke rehabilitation?

Specific Research Objectives:

To what extent that there is a difference between the effects of dorsal-double-layered 10% circumferential reduction (DD-10), single-layered 10% circumferential reduction (S-10), and single-layered no circumferential reduction (S-0) pressure garment on sensorimotor functions, including motor control, dexterity, muscle tone, pain, self-perceived upper extremity function, and quality of life among stroke patients during the 8 weeks of application (Time 1: Baseline, Time 2: Week 4, Time 3: Week 8)?

## **5.0 Research Objectives**

General Research objectives:

To study the effects of different finger-to-above-elbow (long glove) pressure garment with varying fabric layer and circumferential reduction on sensorimotor functions and quality of life among stroke patients during the 8 weeks of application, alongside exploring the perceptions of stroke patients and treating therapists on various issues relating to pressure garment application in stroke rehabilitation.

Specific Research Objectives:

To determine the difference between the effects of dorsal-double-layered 10% circumferential reduction (DD-10), single-layered 10% circumferential reduction (S-10), and single-layered no circumferential reduction (S-0) pressure garment on sensorimotor functions including motor control, dexterity, muscle tone, pain, self-perceived upper limb function, and quality of life among stroke patients during the 8 weeks of application (Time 1: Baseline, Time 2: Week 4, Time 3: Week 8).

## **6.0 Research Hypotheses**

1. There is a difference between the effects of DD-10, S-10, and S-0 pressure garment on motor control as measured by Fugl-Meyer Assessment of Upper Extremity

(Kaufman et al.) among stroke patients during 8 weeks of application.

2. There is a difference between the effects of DD-10, S-10, and S-0 pressure garment on dexterity as measured by Box and Block Test (BBT) among stroke patients during 8 weeks of application.

3. There is a difference between the effects of DD-10, S-10, and S-0 pressure garment on muscle tone as measured by Modified Ashworth Scale (MAS) among stroke patients during 8 weeks of application.

4. There is a difference between the effects of DD-10, S-10, and S-0 pressure garment on pain as measured by Visual Analogue Scale (Venckūnas et al.) among stroke patients during 8 weeks of application.

5. There is a difference between the effects of DD-10, S-10, and S-0 pressure garment on self-perceived upper extremity function as measured by Disabilities of Arm, Shoulder and Hand (DASH) among stroke patients during 8 weeks of application.

6. There is a difference between the effects of DD-10, S-10, and S-0 pressure garment on quality of life as measured by 36 Item Short Health Survey (SF-36) among stroke patients during 8 weeks of application.

## **7.0 Conceptual Framework**

[figure not shown]

Figure 3. Conceptual Framework

The conceptual framework is guided using the ICF model, and the impacts of stroke are mainly reflected in two aspects, sensorimotor functions and quality of life. The sensorimotor functions specifically include motor control, dexterity, muscle tone, pain, self-perceived upper extremity function and the quality of life. External factors are the different types of pressure garments, i.e., DD-10, S-10, S-0. Human factors are the patient's experiences, needs and challenges, and the clinical value of pressure garment as perceived by the therapists. These external and human factors interact with each other.

## 8.0 Operational Definitions

Sensorimotor functions refer to the perception of sensory functions, including pain and motor functions, including motor control, dexterity, and self-perceived upper extremity function of a stroke patient as measuring by Visual Analogue Scale (Venckūnas et al.), Fugl-Meyer Assessment (Kaufman et al.) of upper extremity, Box and Block Test (BBT), Modified Ashworth Scale (MAS), and Disabilities of the Arm, Shoulder and Hand (DASH), respectively.

Quality of life refers to the ability of a stroke patient to perform various tasks in daily lives, including self-care, walking, socialization, and the negative impact of stroke on the patient's physical and mental health, including fatigue and mood disorders, reflected as the overall satisfaction with life that the stroke patient feels physically, mentally, and socially as measured by the 36-item Short Form Health Survey (SF-36).

## **9.0 Research Methodology**

### **9.1 Multicentre, Double-Blind, Prospective Randomised Controlled Trial** (Research Question 1; Specific Objective 1; Hypotheses 1 to 7)

#### **9.1.1 Research Design**

Multicentre, double-blind, prospective randomised controlled trial will be used as it involves three research locations, blinding of participants and therapists, and prospective randomization of the participants into different intervention groups or placebo group.

#### **9.1.2 Participants**

Stroke patients who are admitted to a rehabilitation department of a hospital for rehabilitation services.

##### **9.1.2.1 Inclusion and Exclusion Criteria**

Inclusion criteria:

1. Between 18 and 80 years of age
2. Within 1 – 12 months of ischemic or haemorrhagic stroke
3. First onset resulting in hemiparesis of a limb with Brunnstrom Recovery Stage (BRS)

of 3, 4 or 5 (Naghdi et al. 2010)

4. Modified Ashworth Scale (MAS) with scores of less than or equal to level 2 for elbow, wrist, and hand muscle tone in the affected upper extremity (Harb & Kishner 2022)

5. Able to understand instruction

Exclusion criteria:

1. Serious cardiovascular or respiratory diseases
2. Skin lesions, infections or other skin problems
3. Serious circulatory problems such as deep vein thrombosis
4. Allergies or significant discomfort to pressure garment materials
5. Upper extremity fractures or severe joint problems
6. Severe cognitive impairment with Saint Louis University Mental Status (SLUMs) scores equal to or less than 27 (above high school level of education)/25 (below high school level of education).

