#### **9.1.2.3 Sample Size Calculation**

Sample size was calculated using G\*Power 3.1. Assuming that the data is normally distributed, this study will use mixed model ANOVA to compare differences between

the effects of DD-10, S-10, and S-0 pressure garment on sensorimotor functions and quality of life among stroke patients at three different time points during the 8 weeks of application. With small to medium effect size,  $f$  of 0.125, power of 0.8,  $\alpha$  error of 0.05, three groups, and three measurements, the total sample size needed will be 132, as shown in Figure 4. With 44 people in each group and taking into account the 20 % dropout rate, by using the formula:  $N = n/(1-d)$ , i.e.,  $44/(1-0.2) = 55$ , there will be a total of 55 people in each group. Thus, the final sample size will be 165 patients ( $n$ : DD-10 Group = 55; S-10 Group = 55; S-0 Group = 55).

[figure not shown]

Figure 4. Sample Size Calculation

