| 17:00 – 17:30 | Q&A                                                                                 |

For randomization purposes, the researcher will generate 165 sequences that contains equal numbers of 1 (S-10), 2 (DD-10), and 3 (S-0) using a computerized software SPSS 26.0. The sequence will be store electronically. The process of data

collection will then proceed with participant recruitment. This recruitment will be done by placing posters that contain the relevant information of this study, including the study objectives, procedures, and duration alongside contact information, etc. in the three hospitals as permitted. Interested patients can contact the researcher of this study. Recruitment will also be done through recommendation made by therapists who are involved in treating stroke patients. Before enrolling into the study, potential participants will be screened using MAS, SLUMS, and BRS by Therapist A. Only those who meet the inclusion will be enrolled. Prior to the enrolment, the potential participants will need to read the information sheet (Appendix L) and sign the written informed consent form (Appendix M). Participants will be asked to complete the Demographic Form (Participant) (Appendix A).

After participant enrolment, Therapist A will report to the researcher to obtain the randomization sequence number generated using SPSS 26.0. The researcher will assign the participant into either S-10 (intervention group), DD-10 (intervention group), or S-0 (placebo group) according to the sequence list. Therapist A, a blinded therapist will then proceed with taking the baseline data or Time 1 (start of trial), including FMA, BBT, MAS, VAS, DASH, and SF-36. After that, Therapist A will take the pressure garment measurement and then, give the pressure garment measurement to the pressure garment fabricator for pressure garment custom fabrication. Upon receiving the two pairs of pressure garment (within 7 days after pressure garment measurement), the participant will try it on for 30 minutes, under the supervision of Therapist B, a blinded therapist. The participant will formally be enrolled in the study if he/she does not experience allergy, oedema, pain or any other discomfort. All participants will be asked to wear the provided pressure garment for 3 hours in the morning, 3 hours in the afternoon, and 8 hours at night each day for 8 weeks.

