### **9.1.6 Data Analysis**

Data will be analysed using SPSS 26.0 using Intention-to-treat (ITT) analysis. ITT analysis, which aims to minimize bias and maintain random allocation of study participants (Gupta 2011), is suitable to be used when there are shedding participants. Its key idea is to analyse the group to which the participant belongs in that initial allocation, regardless of whether they completed the study or received the intended intervention. In clinical trials, participants may drop out, refuse intervention, or deviate from the study protocol. The ITT analysis includes all participants regardless of whether they completed the study or followed the treatment plan. This helps prevent shedding bias, which may occur if only completers are analysed (Mccoy 2017). The study will use a imputation method, such as, Last Observation Carried Forward (LOCF) (Shao & Zhong 2003) or mean imputation (Jadhav et al. 2019), or multiple imputation (Austin et al. 2021), this will probably depend on the requirements of the data.

Both descriptive and inferential statistics will be used. Frequencies, means, and medians will be used to describe the demographic data (Fisher & Marshall 2009). A mixed model ANOVA to compare the outcome measures.

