**Appendix A Demographic Form (Participant)****Participant ID:****Date:**

| Demographic Form (Participant)                     |                       |
|-----------------------------------------------------------|-----------------------|
| Personal Information                               |                       |
| 1. Participant ID:                                 |                       |
| 2. Age:                                            |                       |
| 3. Gender:                                         | Male/Female    |
| 4. Hand Dominance:                                 | Right/Left     |
| 5. Affected Hand:                                  | Right/Left     |
| 6. Contact address:                                |                       |
| 7. E-mail address:                                 |                       |
| 8. Telephone number:                               |                       |
| 9. Emergency contact name:                         |                       |
| 10. Emergency contact phone number:                |                       |
| Medical Information                                |                       |
| 1. Date of stroke:                                 |                       |
| 2. Type of stroke:                                 | - Ischaemic stroke    |
|                                                           | - Haemorrhagic stroke |
| 3. Whether received pressure garment intervention: | Yes/No         |
| 4. Hours per day of occupational therapy           |                       |
| 5. Name of therapist                               |                       |
| Intervention                                       |                       |
| 1. Physiotherapy                                   |                       |
| 2. Occupational therapy                            |                       |
| 3. Traditional Chinese Medicine (TCM)              |                       |
| 4. Other treatments                                |                       |
| Lifestyle and Social Background                    |                       |
| 1. Marital status:                                 | - Single              |
|                                                           | - Married             |

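### Time since stroke (1 to 12 months at entry) is neither a stratification factor nor a named covariate, which costs precision in the group-by-time comparison but does not bias it

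*Protocol*

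**What the plan says.** - **Entry window.** Protocol 9.1.2.1 admits patients "Within 1 – 12 months of ischemic or haemorrhagic stroke".
- **Allocation.** In Protocol 9.1.5, "the researcher will generate 165 sequences that contains equal numbers of 1 (S-10), 2 (DD-10), and 3 (S-0"), and each patient is assigned "according to the sequence list". No stratum of any kind is named.
- **Analysis.** Protocol 9.1.6 states: "A mixed model ANOVA to compare the outcome measures". Section 9.1.2.3 sizes the trial on the same model, with effect size f "of 0.125, power of 0.8" and "error of 0.05, three groups, and three measurements". Neither section names a covariate.
- **Data.** The first medical item on the Appendix A form is "Date of stroke". Under 9.1.5 this form is completed around enrolment, before the allocation number is requested.

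**The concern.** The objectives concern change in motor and other outcomes over 8 weeks, so the test of interest is group by time. Patients who enter one month after a stroke may improve at a different rate over those weeks from patients who enter at eleven months, whatever garment they wear. The repeated-measures structure removes stable differences in level between patients. It does not remove differences in rate of change. Two patients with the same baseline Fugl-Meyer score but different times since stroke may still have different expected gains, so baseline score alone would not stand in for time since stroke.

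Two things are at stake. Variance that a recorded baseline variable could explain stays in the error term. And if the arms happen to differ in time since stroke, the stated model does nothing to correct the estimate for it.

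**Working it through.** **1. The plan's own figure.** I used the repeated-measures within-between interaction test. Within-patient correlation rho = 0.5 and epsilon = 1 are my assumptions, because the text of 9.1.2.3 does not state them.

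- lambda = f² × N × m / (1 − rho) = 0.125² × 132 × 3 / 0.5 = 12.375
- df1 = (3 − 1)(3 − 1) = 4; df2 = (132 − 3)(3 − 1) = 258
- Power = 0.808

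The smallest multiple of 3 that reaches 0.80 is 132, as stated. The alternative tests do not reproduce it: the within-subject main effect gives 105 and the between-group main effect gives 417. Dropout: 44 / (1 − 0.2) = 55 per arm, 165 in total. The stated size therefore reproduces, for an unadjusted interaction test.

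**2. What adjustment would gain.** Let r be the correlation between time since stroke and change in outcome, acting on the error variance of the interaction. The effective effect size becomes f / √(1 − r²), so lambda becomes 12.375 / (1 − r²).

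| r (assumed) | lambda at N = 132 | Power at N = 132 | N for 80% power |
|---|---|---|---|
| 0 | 12.375 | 0.808 | 132 |
| 0.1 | 12.5 | 0.812 | 129 |
| 0.2 | 12.9 | 0.826 | 126 |
| 0.3 | 13.6 | 0.848 | 120 |
| 0.4 | 14.7 | 0.878 | 111 |
| 0.5 | 16.5 | 0.916 | 99 |

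The upper rows of r can be illustrated, again only by assumption. Suppose natural 8-week gains of 8 to 12 Fugl-Meyer points at one month, decaying with a 4-month constant, and a residual SD of change of 5 to 7 points. Time since stroke then explains about 8% to 28% of the variance of change, so r is √0.08 = 0.28 to √0.28 = 0.53.

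**3. How large a chance imbalance can be.** If time since stroke is uniform over 1 to 12 months (assumption), its SD is 11 / √12 = 3.18 months.

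- 44 per arm: SE of the difference between two arms = 3.18 × √(2/44) = 0.68 months, 95% within ±1.3
- 55 per arm: 3.18 × √(2/55) = 0.61 months, 95% within ±1.2

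The resulting shift in an arm difference has SD r × √(2/44): 0.06 outcome SD at r = 0.3 and 0.11 at r = 0.5.

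**4. Bias and type I error.** Null simulation, 44 per arm, 5,000 runs at each r:

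| r | Mean unadjusted difference (SD units) | Type I error, unadjusted | Type I error, adjusted |
|---|---|---|---|
| 0.3 | −0.001 | 5.2% | 5.0% |
| 0.5 | 0.004 | 4.8% | 4.7% |

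Under the assumed recovery curves, with two distributions of time since stroke and 44 or 55 per arm (16 settings), unadjusted type I error was 4.1% to 5.5%. There is no bias and no inflation.

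**5. Error given the imbalance that occurs.** If two arms differ in time since stroke by z standard errors, the unadjusted pairwise statistic is approximately normal with mean r × z and variance 1 − r² under the null. The false-positive rate is then:

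| z | r = 0.3 | r = 0.5 |
|---|---|---|
| 1.64 | 6.7% | 9.5% |
| 1.96 | 7.9% | 12.9% |

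A gap of at least 1.64 SE arises in about 10% of trials for a given pair. With no imbalance the rates fall below 5%: 1.96 / √(1 − r²) is 2.05 at r = 0.3 and 2.26 at r = 0.5, giving 4.0% and 2.4%. Averaged over all imbalances, the rate returns to 5%.

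**The case against.** **The test already carries this uncertainty.** This is correct. A reader might infer that mixing early and late patients biases the garment comparison, or that a garment effect could not be told apart from an arm with more recent strokes. The documents do not support that. Allocation is random, so chance imbalance is part of the error that the p-value and interval already reflect, and the simulations confirm it. What remains is precision, together with error conditional on an imbalance that can be seen once the patients are enrolled.

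**Covariates are usually left to the SAP.** This largely stands. An SAP may exist, and 9.1.6 does not rule out adjustment, so its silence is weak evidence. The allocation method is different: 9.1.5 describes it fully, without strata, and it cannot be changed after enrolment.

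**The date of stroke is not ignored.** This is fair. Section 9.1.6 will describe the demographic data, and time since stroke can be tabulated from it. Tabulating does not adjust.

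**The gain may be small and rests on outside assumptions.** This stands. The documents give no recovery curve, no SD of change, no distribution of time since stroke and no r. At r = 0.1 the gain is about 0.4 percentage points of power.

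**Conclusion.** The point holds as one of efficiency. A wide entry window, a list without strata and a named model without covariates leave a recorded and plausibly prognostic variable out of both design and analysis. The gain from using it runs from negligible at r = 0.1, through about 4 percentage points of power at r = 0.3, to about 11 at r = 0.5. These figures are all at N = 132, with rho = 0.5 and epsilon = 1 assumed and r treated as acting on the interaction error variance. That recovery rate depends on time since stroke is itself an assumption here. The validity of the comparison is not in question. Severity is minor to moderate; the change is worth making because it is nearly free and the trial is planned at only 0.80 power.

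**What to change.** In 9.1.6 (or in the SAP, if there is one), prespecify time from stroke to Time 1, in log months from the Appendix A date, as a baseline covariate for the Fugl-Meyer score and the other motor outcomes. Either enter it with its interaction with time, or use it as a covariate in the week-8 comparison. A main effect alone would leave the group-by-time test unchanged. The cost is one sentence and one or two degrees of freedom, against 258 error degrees of freedom in the planned interaction test. No new data are needed.

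If the list has not yet been generated, it could also be permuted in blocks within early and late strata, for example 1 to 3 months and over 3 to 12 months. The stratum is known at allocation because eligibility depends on it. The list becomes slightly more complex, and because stratum sizes are not known in advance, exactly 55 per arm could no longer be guaranteed. This step is optional; the covariate recovers most of what is at stake.
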